### Participants

Each participating practice will identify two champions. One will be a clinician; the other could be anyone in the practice, including nonclinical staff, who could work regularly with a registry should one be implemented. Clinician champions must meet the following criteria: the clinician must be a medical doctor, doctor of osteopathy, physician assistant, or nurse practitioner; have their principal employment in the practice; be authorized to lead a practice improvement process; and regularly provide care to patients with type 2 diabetes.

### Intervention activities

Intervention and control practices will differ in the level of support and type of resources offered by the research team. All practices will participate in champion meetings at least twice during the project period. All practices will receive basic technical assistance if they are unable to identify their total patient population with type 2 diabetes. In addition to these activities, however, intervention practices will be paired with peer mentors and will be given access to continuing basic technical assistance offered by a physician informaticist with expertise in primary care data systems and reporting. Following the recommended criteria for specifying and reporting implementation strategies put forth by Proctor and colleagues, we specify the operationalization of our SPARC implementation strategy in Table 1 [42]. Next, we provide details of these project elements.

**Table 1 Tab1:** **Specification of the SPARC intervention strategy**

**Specification domain**	**Specification of intervention strategy**
Actors	Peer mentors: clinicians who have implemented and maintained a diabetes registry in their practice
	Physician informaticists: clinicians with expertise in primary care data systems and reporting
Actions	1) Two champion meetings
	• Provide education to intervention and control practices on how to implement a diabetes registry, including:
	− Registry development
	− Population health in primary care delivery
	− The American Diabetes Association’s guidelines for patients with diabetes
	− Diabetes registry software options or communicating with EHR vendors about registry functionality
	− A practice self-assessment checklist designed to help practices plan and manage potential workflow changes
	• Facilitate discussion among intervention practices about the challenges faced during registry implementation and solutions developed to overcome those challenges
	• Provide intellectual space for intervention practices to process what they are learning and talk about their experiences with registry implementation, as well as develop a plan for sustaining or expanding their registry
	2) Peer mentoring
	• Advise intervention practices on registry implementation and using the materials disseminated at champion meetings.
	• Provide intervention practices with access to physician informaticists to assist with use of practice data systems.
Target of the actions	Practice champions: two champions from each intervention and control practice—one clinician champion and one champion who will be a potential user of a registry—will attend the champion meetings. Champions in intervention practices will work with the peer mentor.
Temporality and dose	1) Champion meetings
	• One champion meeting will be held before the intervention period and a second about 15 months later.
	2) Peer mentoring
	• Peer mentors will work with practice champions in intervention practices for the first 12 months of the intervention, maintaining monthly communication through telephone calls and practice visits.
Implementation outcome(s) effected	Change in mean patient hemoglobin A1c scores
Justification	We believe that helping practices use existing resources and learn how to solve problems to implement a diabetes registry and related workflow changes will be more sustainable than implementation strategies that rely more heavily on external resources.

### Champion meetings

Two champion meetings will be held for all participating practices. Control practices and intervention practices will meet separately. The first champion meeting will be largely the same for control and intervention practices. These meetings will provide an opportunity for participants to learn about diabetes registries, workflow redesign, and general principles regarding population-based approaches to care delivery for patients with chronic conditions. Participants will be introduced to a practice self-assessment checklist tool, designed during the R34 pilot project, to help practices plan workflow changes and registry goals. They will gain insights into what they need to discuss with their EHR vendor to make the registry work and will learn about software options available if their current EHR does not support a registry function. Champions will be introduced to the SPARC research team and will provide basic baseline demographic information on their practices and mix of patients. They will leave the meeting with a packet of information that includes the American Diabetes Association’s guidelines for patients with diabetes.

In addition to the champion meeting elements, intervention practices will receive two pieces of information not shared with control practices. First, they will be introduced to their peer mentors and will receive a document outlining basic implementation milestones (described below and in Additional file 1). Second, they will be introduced to a physician informaticist who will be available to them by telephone to answer basic questions during the study.

At the second champion meeting, 15 months later, participants will discuss the challenges they faced during registry implementation and solutions they developed to meet those challenges. This meeting will provide intellectual space for practices to process what they have learned and how they have changed during registry implementation. The research team will share preliminary findings from the first year with study participants. These will include patterns identified in the qualitative data by research analysts and changes in chart audit data from baseline to year 1. Practice members will be invited to help explain the significance of those findings. They will also be led in a discussion regarding plans to sustain, and for some expand, their now-existing registry.

### Peer mentors and physician informaticists

Peer mentors, available only to the intervention practices, are practicing clinicians who have successfully implemented and maintained a diabetes registry in their practice. The peer mentors will attend the first champion meeting for intervention practices to present information on registry development and answer questions about it. After the meeting, clinician champions from intervention practices will be paired with a peer mentor who will advise them on the use of the self-assessment tool and will offer basic guidance regarding workflow redesign. Peer mentors will visit each intervention practice at least twice during the first study year: once at baseline and once shortly after the practice begins using the registry. In between these visits, peer mentors will call practice-level champions in the intervention practices monthly to monitor implementation progress, offer assistance, and help the practice connect to basic technical assistance from the physician informaticist if needed. Practice-level champions can contact the peer mentors by telephone or email throughout the intervention period.

Some practices will be able to adopt registries successfully with little additional support; others may need some limited technical assistance or guidance. Peer mentors will tailor their efforts to specific practice situations to meet these varied needs. The mentors’ decisions regarding the need for additional in-person visits or more frequent telephone contact will be guided by the SPARC Milestones document, which outlines eight critical steps in the meaningful adoption of a diabetes registry (see Additional file 1). This document will also be shared with intervention practices during the first champion meeting. Peer mentors will use this document to assess monthly implementation progress for each intervention practice and determine whether a specific practice needs additional support.

Peer mentors will identify practices that would benefit from assistance from a physician informaticist as they implement their registry. The physician informaticists are primary care physicians with experience and expertise in primary care data systems and reporting who will be available to help practice champions with such tasks as querying existing records to populate stand-alone registry systems, identifying changes to work processes to ensure structured data entry of specific fields needed to populated integrated registry systems, and developing reports based on registry data.

An activity log of peer mentor and physician informaticist contacts and provision of basic technical assistance will be maintained to assess the level of effort provided to participating practices. These work logs will inform the cost and cost-effectiveness evaluation of the intervention, as described below.

### Data collection

SPARC researchers will collect data using mixed-methods explanatory sequential design [43]. In such a design, data collection happens in iterative cycles during which preliminary findings from one set of data influence data points collected in the next set of data. For example, findings during a chart audit review might identify the need for collection of qualitative data elements not previously identified, so that the significance of chart audit findings might be better understood. Data collected in SPARC will include medical record review, cost data, participant observations, key informant interviews, and in-depth interviews with practice champions and project leads [44]. Data collection will occur at baseline, 12 months post-registry implementation, and 24 months post-registry implementation. We understand it is possible that not all practices will successfully implement a diabetes registry and that some control practices may implement a registry without assistance. Based on our findings from the R34 pilot study, initial adoption of a registry will take up to 3 months. We will use medical record reviews (described in the next section) to collect patient outcome data (mainly hemoglobin A1c) with which we will evaluate the effectiveness of the registry. Data collected during qualitative site visits (described below) will allow SPARC researchers to evaluate the contextual factors and practice characteristics associated with successful implementation of a diabetes registry, including any barriers or problem-solving strategies that practices employ to enable registry implementation. During qualitative site visits, we will also collect information related to cost of the intervention in each practice.

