### Foundational research

Critical elements of the SPARC intervention were first identified through two previous studies. The Translating Research Into Action for Diabetes study found that improvements in processes of diabetes care (such as ensuring routine, periodic measurement of A1c) were not necessarily associated with improvements in intermediate clinical outcomes (such as A1c levels). Therefore, practice-level efforts to improve care for patients with diabetes will need to move beyond ensuring adequate monitoring alone to a more proactive focus on improving the management of care and appropriate treatment intensification for these patients—that is, a focus on acting on those measurements, when appropriate [37-39]. In addition, we pilot tested the feasibility of a low-cost approach to facilitate diabetes registry implementation and use through the Organizational Self-Assessment to Improve Diabetes Care in Primary Care Practices (R34DK075417) study, referred to hereafter as the R34 pilot study or the R34 study. In that study, six primary care practices worked to implement and use a diabetes registry. Four practices successfully implemented a diabetes registry and increased the percentage of their patients with HbA1c ≤ 7.0 from 77.4 to 79 (*p* = 0.001), with nonsignificant improvements in the percentage of patients with appropriate control of LDL and blood pressure.

Since the completion of the prior pilot study, there have been advances in EHR capabilities, and their use has continued to increase among primary care practices. For example, EHRs certified by the Office of the National Coordinator for Health Information Technology as meeting the standards for the Meaningful Use program sponsored by the Centers for Medicare and Medicaid Services must have registry functionality available as either a built-in function or an add-on module [40]. Therefore, practices participating in SPARC may be able to use EHR-based registry functions not available at the time of the previous pilot study. If participating SPARC practices have an EHR with registry functionality, the SPARC research team will encourage them to use that function. Otherwise, the research team will offer information on how to use a free manual registry software program.

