### Setting and recruitment

The intervention will target 30 Virginia internal medicine and family medicine practices participating in the Virginia Ambulatory Care Outcomes Research Network (ACORN) [41]. ACORN, sponsored by VCU, is a practice-based research network of nearly 100 primary care practices. Member practices are in rural, urban, and suburban settings and range from single-clinician practices to large practice groups and hospital-owned clinics. ACORN member practices choose which studies to be involved in and receive no specific benefit as part of their membership, other than the opportunity to contribute to advancing the science of primary care.

Practices eligible to participate in SPARC must meet the following criteria: (1) the practice must treat adult patients with type 2 diabetes, (2) the clinicians and staff in the practice must be able to change workflows in support of the intervention, and (3) the practice must have a clinician champion who can attend champion meetings (described below) and lead registry implementation in the practice. Practices already using a registry or those that do not currently use an EHR are excluded from participation.

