### Qualitative site visits

SPARC researchers will visit each participating intervention and control practice to assess practice organizational characteristics and workflow related to care of patients with diabetes. Site visits will be conducted at three points during the study: at baseline, 12 months, and 24 months.

Researchers will use four primary methods for data collection during the site visits: participant observation, key informant interviews, cost survey instruments, and semistructured clinician interviews. Participant observations will consist of three to four observation periods in each practice, each period lasting 3 to 5 h. Observations will be guided by an observational template developed during the R34 pilot study and refined for use in this project. SPARC researchers will observe practice workflow, care delivery, and check-in processes, with special attention paid to diabetes-specific and registry-specific activities. During observations, researchers will identify two or three practice members for interviews to learn more about workflow changes in registry implementation. Qualitative site visits will also include interviews with practice managers or administrators to collect cost data relevant to registry implementation.

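### The Data collection section times follow-up from registry implementation, a post-randomisation event that some practices will not have, and this conflicts with the plain 12- and 24-month schedule elsewhere

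*Protocol article*

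**What the plan says.** The Data collection section lists the data to be gathered, including the medical record reviews that supply hemoglobin A1c, and then sets the timing: "Data collection will occur at baseline, 12 months post-registry implementation, and 24 months post-registry implementation". It is the only sentence in the article that names a time origin for follow-up. The next sentence accepts that "not all practices will successfully implement a diabetes registry and that some control practices may implement a registry without assistance", and the one after it, citing the pilot, that "initial adoption of a registry will take up to 3 months". No date is given for a practice that never adopts.

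Elsewhere the schedule carries no such anchor:

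- The Abstract (Methods) gives baseline, 12 and 24 months for control and intervention practices alike.
- Sample size and power analysis gives 1- and 2-year intervals for each of the 30 practices.
- Medical record reviews gives 12 and 24 months for each participating practice.
- Qualitative site visits: "Site visits will be conducted at three points during the study: at baseline, 12 months, and 24 months".
- Statistical analysis makes the primary comparison the change in A1c from baseline to year 1 between arms. Time is a two-level indicator, and practices are analysed by allocated group regardless of compliance.

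**The concern.** Implementation is a poor time origin for a randomised comparison, for three reasons.

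1. It always falls after entry. Under Setting and recruitment, "Practices already using a registry or those that do not currently use an EHR are excluded from participation".
2. Whether and when it happens is what the intervention is meant to change, so the measurement date can depend on arm.
3. Some practices will never reach it, and for them the rule produces no date at all.

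The primary analysis needs a comparable year-1 measurement from every practice in its allocated group. If the sentence were followed, non-implementing practices would have no scheduled year-1 review, which sits badly with intention to treat. Implementing practices would be reviewed later than 12 months, and the model holds no term for actual elapsed time. Two teams working from this article could schedule the primary outcome differently.

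**Working it through.** **The plan's own figure, used here only as a yardstick.** Inputs from Sample size and power analysis: SD 1.6, ICC 0.065, 100 records per practice, and 24 practices after dropout (12 per arm). Two-sided 5% significance is assumed.

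- Design effect: 1 + (100 − 1) × 0.065 = 7.435
- Effective number per arm: 12 × 100 / 7.435 = 161.4
- Power for a difference of 0.5, comparing follow-up means: 80.2%

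This matches the stated 80%. The figure is not in dispute; it confirms 0.5 as the effect against which to judge a timing error.

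**Practices without a year-1 date on the literal reading.** Foundational research reports that in the pilot "six primary care practices worked to implement and use a diabetes registry", and that four succeeded.

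- Intervention arm at the pilot rate: 15 × 4/6 = 10 implement and 5 do not.
- Control arm: no adoption rate is given. If c of the 15 controls adopt, 15 − c have no date.
- Total without a date: 5 + (15 − c). This is 20 of 30 if c = 0, 15 if c = 5, and 10 if c = 10 (the pilot rate in both arms).

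**Timing for practices that implement.** A lag of up to 3 months, counted from the start, puts the reviews at up to 12 + 3 = 15 and 24 + 3 = 27 months. The first interval is up to 3/12 = 25% longer.

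**Effect on the primary contrast.** This needs three assumptions that the article does not make: non-implementers are measured at 12 months, no control adopts, and A1c drifts by 0.1 to 0.3 points a year.

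- Mean offset between arms, with all 10 implementers at the maximum lag: (10 × 3 + 5 × 0)/15 − 0 = 2 months
- Shift in the between-arm change: 0.1 × 2/12 = 0.017, to 0.3 × 2/12 = 0.05 points
- Share of the 0.5 target: 0.017/0.5 = about 3%, to 0.05/0.5 = 10%

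Shorter lags, or adoption by some controls at a similar lag, make the offset smaller.

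**The case against.** The strongest reply is that this is one loosely worded sentence in a condensed article. Every other section gives ordinary elapsed time, and several name both arms or every practice. The sentence after the disputed one itself anticipates non-adopters. At the second champion meeting, about 15 months after the first, the team is to present "changes in chart audit data from baseline to year 1", which fits reviews at about 12 months from the start better than reviews due as late as month 15. On that view no practice would go unmeasured.

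Much of this stands. Time from baseline is the likely intent, so a reader should not infer that the trial will in fact compare the arms at different times. Nor do the documents support saying that most controls would lack a date. No control adoption rate is given, and controls also receive registry education, a planning checklist and advice on software and EHR vendors. A reader might also apply the full 3-month lag to the arm contrast. That would require all 15 intervention practices to adopt at the maximum lag and no control to adopt, which is inconsistent with using the pilot rate of 4 in 6.

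The reply does not rescue the sentence. The other sections imply a baseline origin but do not state one, and none overrides the only origin that is stated.

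**Conclusion.** The concern holds as an internal contradiction in which the one explicit rule is unworkable as written. The decisive defect needs no assumption: the rule gives no year-1 date to practices that do not implement, and the article concedes there may be such practices. The count of about 5 of 15 intervention practices rests on a pilot of six, and registry functions in EHRs have advanced since then; the control count is unknown. The drift bias is secondary. At 0.017 to 0.05 A1c points it is small against the 0.5 target, and it depends on an assumed trend, the maximum lag and an unstated fallback to 12 months. The intention-to-treat rule is clearly stated and is not itself wrong; the timing sentence is what fails to serve it.

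**What to change.** In Data collection, delete *post-registry implementation* in both places. State that record reviews and site visits take place at 12 and 24 months from one origin that does not depend on adoption, in all 30 practices.

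The origin can be each practice's own baseline review date or a common calendar date. A practice's own date keeps its interval at 12 months, although a small calendar difference between arms may remain. The first champion meeting is not a suitable common origin: the arms meet separately, and Trial status schedules the control meeting first, in March 2015, with the intervention meeting afterwards.

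Record each practice's registry adoption date separately, as an implementation measure.

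The cost is wording and scheduling, with no extra visits. Trial status shows that baseline collection had not begun when the article was written, so the change could be made before any follow-up.

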### Medical record reviews

We will review the medical records of 100 randomly selected patients with diabetes from each participating practice to assess diabetes care quality at baseline, 12 months, and 24 months. These records will be selected from lists generated by practices at the start of the study period, as well as at each subsequent review point, of all patients with a visit coded with an ICD diagnosis code for type 2 diabetes, excluding any patients who are pregnant, under age 18, or over age 75. A trained medical record reviewer will visit practices to conduct reviews; reviews will be done with a structured abstraction or audit instrument. To provide quality assurance, a different staff member will review 10% of the already reviewed records. Medical record reviews will be standardized across all practices. In addition, each review may include up to five questions added at the participating practice’s request. During practice recruitment, practices were able to review the standardized chart review instrument and suggest additions most beneficial to their setting. If practices requested additional items, those items are added to the review of their practice information only. Data from medical record reviews will be directly entered into the study database using an electronic tablet-based instrument designed in SharePoint. In addition to data specified by the audit form, medical record reviewers will take notes regarding where in the record information was found and at what level of standardization within the practice.

